## e) Equipment to be used for assessing the clinical investigation variables

### Functional performance testing

Functional balance will be examined. Table 2 lists the different tests. A 6-min walking test, dual-task L-test, L-test, slope walking test, and stairs climbing and descending test will indicate functional balance and dual-task performance. Rating of perceived exertion [16], level of fatigue and comfort [17] and NASA-Task Load index (NASA-TLX) assessing perceived workload [18] will be assessed after each task.

| Performance tests                       | Outcome                       | Materials                   |
|-----------------------------------------|-------------------------------|-----------------------------|
| Slope walking test [19]                 | Time to complete test         | Stopwatch                   |
|                                         | Biomechanical gait parameters | Inertial measurements units |
| Stair climbing and descending test [20] | Time to complete test         | Stopwatch                   |
|                                         | Biomechanical gait parameters | Inertial measurements units |
| Dual-task L-test [21]                   | Time to complete test         | Stopwatch                   |
|                                         | Accuracy of subtractions      | Audio-recorder              |
| L-test [21]                             | Time to complete test         | Stopwatch                   |
| 6-min walking test [5]                  | Distance covered in 6 minutes | Measuring wheel             |
|                                         | Biomechanical gait parameters | Inertial measurements units |

Table 2: Physical performance tests

The primary endpoint is the distance covered during the 6-min walking test. Any difference found between the different prostheses on the distance travelled will be considered clinically relevant from a difference of 35 metres [5]. Secondary endpoints will comprise performance on the L-test, dual-L-test, slope walking test and stairs climbing and descending test, and the evaluation of the gait pattern.

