### Structural brain adaptations using MRI

Structural whole-brain networks changes will be researched by applying different MRI techniques during pre, mid, and post-test assessment. MRI-assessment is part of the clinical investigation of WP1. An MRI scan will be conducted to gather an anatomical scan comprising different sequences on a 3-Tesla MRI-unit. A 30-minute protocol will be followed, compiled out of scout images, 3D T1-weighted spin-echo images, diffusion-weighted imaging HARDI and an optional 3D MAGIC. These measurements will consequently be used to determine whole-brain networks based on the cortical and subcortical regions of interest [23][24]. Regions of interest will include the primary motor cortex, primary somatosensory cortex, premotor cortexes, supplementary motor area, corpus callosum, basal ganglia, thalamus and cerebellum as they are responsible for motor control and balance.

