### b) Descriptive statistics of baseline data

#### *Functional performance testing*

A mixed model will be constructed enabling within and between group (i.e., type of prosthesis) comparison of balance performance and accounting for baseline covariates. If residuals are not normally distributed, required adaptations to the data or model will be performed. To correct for multiple comparisons, suited corrections will be applied. The factors age, time since amputation, side of amputation, level of amputation, time using prosthesis, previously used prosthesis will be accounted for. Statistical significance level will be set at 5%.

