#### *Structural brain adaptations*

Differences in connectivity between pre-test and post-test assessment, both within and between groups (i.e. type of prosthesis), will be analysed by means of structural equation modelling. This analysis allows to investigate the causal relationships between brain structure and performance indicators while controlling for confounding factors. The factors time since amputation, side of amputation, amputation level, time using prosthesis, previously used prosthesis, age, sex, Mini-Mental State Examination score, and level of education will be accounted for. Statistical significance level will be set at 5%.

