### d) The significance level of the power of primary endpoint(s)

Statistical significance level will be set at 5%.

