The principal investigator and co-investigators will analyse the data independently to identify any error probabilities.

- l) The specification of subgroups for analysis

Not applicable.

- m) Management, justification and documentation of missing data

Drop-outs and unused data will not be included in the analyses. We ensure that any unused or spurious data (including drop-outs) will be fully recorded by the investigators, manufacturer or other parties, and immediately notified to sponsor to all competent authorities (including FAMHP) by using the European form in a timely manner.

- n) Exploratory analysis and sensitivity analysis

Not applicable.

o) Procedures for reporting any deviation(s) from the original statistical analysis plan

We ensure that any deviation will be fully recorded by the investigators, manufacturer or other parties, and immediately notified to sponsor to all competent authorities (including FAMHP) by using the European form in a timely manner.

p) A strategy for handling the potential imbalance of the number of subjects across investigation sites

Not applicable since each subject of this clinical investigation will perform the different experiments in the two same investigation sites.

q) A strategy for pooling data

All data will be entered in excel and physical copies will be scanned as a pdf file. During the investigation, data will be saved on the VUB share point, which has a built-in back-up. After the investigation, data will be anonymized where possible and stored in the VUB university archive.

As personal and sensitive data of human participants will be collected, pseudonymisation of the data will take place as soon as possible upon data acquisition. The file which establishes the link between the pseudonymised identities and the identification of the participant, will be password- protected.

All raw data will be stored in the online system of the Ethical Committee of the UZ Brussel (i.e., Redcap). Raw and cleaned data will also be stored and encrypted on the research's group network attached storage (NAS) under supervision of [name] [name]. The NAS is system-encrypted, back-upped, has up-to-date antivirus and is only accessible by authorised personnel. Passwords will be required to access the NAS, in compliance with the GDPR regulations. All manual files and written data will be stored in locked filing cabinets. All anonymized data will be stored for up to 10 years as recommended by the VUB.

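### Section 7(k) offers duplicate analysis by the investigators as the multiplicity procedure; it controls no error rate, and the brain-connectivity analysis is left with no correction

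*Protocol*

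**What the plan says.** Section 7(k) is headed as the place for multiplicity control and adjustment of error probabilities. Its whole content is one sentence: "The principal investigator and co-investigators will analyse the data independently to identify any error probabilities". It names no adjustment, family of tests, hierarchy or division of alpha, and it does not refer to another section or to a later plan.

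Other sections bear on the same point:

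- **Section 6.1(e), functional testing.** "The primary endpoint is the distance covered during the 6-min walking test". "Secondary endpoints will comprise performance on the L-test, dual-L-test, slope walking test and stairs climbing and descending test", and evaluation of the gait pattern is added to these.
- **Section 7(b), functional testing.** A mixed model is planned. "To correct for multiple comparisons, suited corrections will be applied". The correction and its family are not named. The model may change with the data: "If residuals are not normally distributed, required adaptations to the data or model will be performed".
- **Section 7(b), structural brain adaptations.** Connectivity differences between pre-test and post-test, within and between groups, "will be analysed by means of structural equation modelling" at a 5% significance level. No correction is mentioned.
- **Section 6.1(e), MRI.** "Regions of interest will include the primary motor cortex, primary somatosensory cortex, premotor cortexes, supplementary motor area", followed by corpus callosum, basal ganglia, thalamus and cerebellum.
- **Section 7(d).** The significance level is 5%.
- **Section 14(j).** Co-investigators analyse the data and the principal investigator controls this for the sponsor.

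**The concern.** This is not a detail left to a statistical analysis plan. The protocol fills in the entry, and what it states cannot do what the heading asks. Multiplicity control limits the chance of false claims across several tests. Having more people run those tests leaves that chance where it was.

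Three consequences follow.

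1. H2, the brain-network hypothesis in Section 5(d), is tested at 5% within and between groups with nothing to limit false positives over the comparisons drawn from the model.
2. The secondary functional tests are protected only if the promise in Section 7(b) is carried out. Section 7(k), where a reader would look for it, does not mention that promise.
3. Independent analyses with an adaptable model can give different answers, and nothing says which one is reported.

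**Working it through.** The protocol derives no error-rate figure that could be reproduced; the 5% is simply set. The check compares the sections and then illustrates the size.

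**Step 1: what 7(k) does to the error rate.** For m independent tests, each at level α, the probability of at least one false positive is 1 − (1 − α)^m. The number of analysts does not enter. If all analysts run the same analysis, each test keeps its 5% level and the family-wise rate is the same as with one analyst.

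**Step 2: the sections side by side.**

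| Analysis | Level | Correction stated |
|---|---|---|
| Primary, 6-minute walk distance | 5% | None needed for one endpoint and one between-arm contrast |
| Secondary functional endpoints | 5% | Promised in 7(b), not named |
| Brain connectivity, within and between groups | 5% | None |
| Section 7(k), meant to cover the whole plan | – | Duplicate analysis only |

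Sections 7(k) and 7(b) give different answers to one question. Sections 7(k) and 14(j) also differ on who analyses: separate analyses by all investigators in one, analysis by some with oversight by another in the other.

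**Step 3: illustration for the MRI tests.** The number of tests to be drawn from the structural equation model is not stated. Eight is taken only because Section 6.1(e) lists eight regions or region groups.

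- Independent: 1 − 0.95^8 = 1 − 0.663 = 0.337, or 34%.
- Equally correlated two-sided normal test statistics: 25% at a correlation of 0.5 and 16% at 0.8, by numerical integration. Both correlations are assumptions; the protocol gives none between outcomes.

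**Step 4: illustration for differing analyses.** Suppose two analysts produce versions of one test whose statistics correlate at 0.95 to 0.80 (assumed), and the more favourable version could be reported. The type I error for that endpoint would be about 6.5% to 7.8%. With identical analyses it stays at 5%. The excess therefore comes from the open model combined with the missing reporting rule, not from duplication itself.

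**The case against.** **Corrections are promised for the functional tests.** This stands. A reader might infer that the four timed secondary tests carry a family-wise error of 1 − 0.95^4 = 18.5%. That follows only if the commitment in Section 7(b) is ignored. Leaving the method to an analysis plan would be ordinary, and Section 7(o) refers to one. What remains is that 7(k) states something else.

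**Independent analysis may just mean a quality check.** This also stands in part. A reader might infer that the protocol sets up rival versions of each result to choose from. It does not say so, and Section 14(j) points towards analysis with oversight. The supportable point is narrower: the model is adaptable and no rule settles a disagreement.

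**The MRI test count is invented.** Correct, which is why the 34% is only an illustration. Taking all pairs of eight regions gives 8 × 7 / 2 = 28 tests and 1 − 0.95^28 = 76%, but the protocol plans one structural equation modelling analysis, not a test per region or pair. The region list is also not worded as a list of tests. Neither percentage is a property of this plan.

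**The primary conclusion is untouched.** Agreed. There is one primary endpoint, and 7(k) does not raise its 5%. A reader who concludes that the main between-arm test is inflated by 7(k) goes beyond the text.

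**Conclusion.** The point holds in this form: Section 7(k) gives a procedure that controls no error rate, does not match Sections 7(b) and 14(j), and leaves the connectivity analysis uncorrected at 5%. It also supplies no rule for which analysis is reported if the independent ones differ.

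The problem concerns H2 and, unless the corrections promised in 7(b) are applied, the secondary functional tests. It does not concern the primary test.

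The size cannot be fixed from the protocol. Roughly 16% to 34% for eight MRI tests shows the order of magnitude and rests on an assumed count, two-sided tests, and correlations from 0.8 down to zero. The fault in 7(k) does not depend on these figures. The change is worth making, and it has most value before any data are seen.

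**What to change.** Replace the text of Section 7(k) with the following elements:

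1. One confirmatory test: the between-arm difference in 6-minute walk distance, at 5%.
2. The correction promised in Section 7(b), by name, with its family. Holm across the declared secondary functional endpoints is one valid choice.
3. Error control for the MRI analysis, for example a 5% false discovery rate across the region or connection tests actually made, with their number stated in advance.
4. One pre-specified, locked analysis as the reported result. Any second analysis only verifies it.
5. Wording on who analyses and who checks that agrees with Section 14(j).

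The gait pattern can stay a declared secondary endpoint; correcting 7(k) does not require calling it exploratory.

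**Cost.** No participants, visits or measurements are added. Thresholds become stricter. With Holm over the four timed tests the smallest p-value must reach 0.05 / 4 = 0.0125; over five endpoints, counting gait pattern as one, 0.05 / 5 = 0.010. With false discovery rate control over eight tests, a lone finding would need p ≤ 0.05 / 8 = 0.00625. With 40 participants with amputation, that is a real loss of power for secondary and MRI results. If the protocol is already approved, the change goes through the amendment route in Section 9.

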## f) Any procedures for the replacement of subjects

Not applicable.

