## h) Definition of completion of the clinical investigation

The clinical investigation will be considered as terminated when the proposed sample size is tested and is defined as the last visit of the last subject.

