### c) Criteria and procedures for subject withdrawal or lost to follow-up

Participants can withdraw at any time without reason from the experiment. In case of subjects drop-out is not met, additional subjects will be recruited via the same rehabilitation centres and orthopaedics departments of hospitals until the sample size is obtained (40 lower-limb amputees and 20 able-bodied subjects).

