## 7. Statistical design and analysis

### a) Analysis population

The entire population enrolled in the study will be included in the analysis.

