### e) Sample size calculation and justification

The primary endpoint of the clinical trial is the distance covered during the 6-minutes' walk test. The sample size was calculated based on a study comparing passive and quasi-passive prosthetic ankles which found an effect size Cohens'  $f = 0.318$  on distance covered during the 6-minutes' walk test [4]. A total of 40 participants with a lower limb amputation is required and will be allocated to one of the two prosthetic groups. These individuals will be stratified by age (2 strata:  $< 45$  years,  $\geq 45$  years, block size = 4) to control for age-related cognitive deterioration. A matched control-group of 20 able-bodied individuals will be included to enable comparison. The required number of 40 participants with amputation is based on a sample size calculation for an analysis of variance using G\*Power (version 3.1.9.4) envisaging 10% drop-out. Values used for this calculation were medium expected effect size  $f = 0.318$ , power = 0.80,  $\alpha = 0.05$ , the number of groups = 3 and the number of measurements set at 2 with a correlation between measurements of 0.75.

- f) The rationale for the number of procedures to be performed by a single user as part of the learning curves

A baseline experiment with a conventional prosthetic ankle used in rehabilitation is required to observe any similarities or differences in outcomes with the LUNARIS®. Moreover, a baseline experiment with able-bodied subjects is required to observe any similarities or differences in outcomes with the LUNARIS®. Therefore, each lower-limb amputee is asked to schedule four appointments and each able-bodied subject is asked to schedule two appointments to run through the whole experiment.

- g) Pass / Fail criteria to be applied to the results of the clinical investigation

Not applicable.

- h) The provision for an interim analysis

Not applicable.

- i) Management of bias

All appointments for the MRI will take place at UZ Brussel to avoid any bias due to a different MRI scanner. All appointments for functional performance testing will take place at Axiles Bionics to avoid any bias due to different slopes or staircases between subjects and between sessions.

- j) Management of potential confounding factors

Not applicable.

- k) Description of procedures for multiplicity control and adjustment of error probabilities

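### The protocol gives opposite rules for analysing and for replacing drop-outs; on one reading the primary comparison becomes a completer analysis that can be biased

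*Protocol*

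**What the plan says.** Five places in the protocol bear on who is analysed.

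- **Section 7 a), analysis population:** "The entire population enrolled in the study will be included in the analysis".
- **Section 7 m), missing data:** "Drop-outs and unused data will not be included in the analyses". The sentence after it says that such data, drop-outs included, will be recorded and notified.
- **Section 6.3 c), withdrawal:** "additional subjects will be recruited via the same rehabilitation centres and orthopaedics departments of hospitals until the sample size is obtained", with the target given as 40 amputees and 20 able-bodied subjects. The condition meant to trigger this does not parse.
- **Section 6.1 f):** under the heading "Any procedures for the replacement of subjects" the answer is that this is not applicable.
- **Section 7 e), repeated in 5 c):** "A total of 40 participants with a lower limb amputation is required", a number reached "envisaging 10% drop-out".

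Section 6.1 h) adds: "The clinical investigation will be considered as terminated when the proposed sample size is tested". Section 7 n) marks exploratory and sensitivity analysis as not applicable. Section 7 b) plans a mixed model for the functional tests. Section 6.1 d) places the first functional tests at week 12 and the second after week 24.

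**The concern.** The contradiction concerns the analysis set of the primary endpoint, the 6-minute walk distance, with 20 amputees per prosthesis group. If it stays open, the rule may be chosen once it is known who dropped out and how far the others walked.

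The content of Section 7 m) matters as well. Drop-out happens after allocation, during 24 weeks on the allocated foot. Dropping those people makes the comparison conditional on having stayed. It also discards the week-12 walk of anyone lost later, although that is a valid measurement of the primary endpoint and a mixed model can use it.

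Unequal loss is plausible from the protocol itself. Section 6.1 d) lets only the comparator group try other devices between weeks 12 and 24. Section 6.2 a) describes the LUNARIS group as using the LUNARIS throughout and mentions no switch. A comparator participant who is unhappy with the foot can change it and remain in the study; a LUNARIS participant may leave instead.

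**Working it through.** **1. The rules side by side, for one amputee who walks at week 12 and is lost before week 24**

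- Section 7 a): analysed.
- Section 7 m): not analysed.
- Section 6.1 f): not replaced.
- Section 6.3 c): apparently replaced, if the target means completers.

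The first two exclude each other, and so do the last two.

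**2. The plan's 40 and the drop-out allowance**

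Completers = allocated × (1 − drop-out): 40 × 0.90 = 36, and back again 36 / 0.90 = 40. So 40 is the inflated number. If recruitment continues until 40 have completed:

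- at 10% loss, 40 / 0.90 = 44.4, so 45 must be enrolled and 5 are not analysed;
- at 20% loss, 40 / 0.80 = 50 must be enrolled and 10 are not analysed.

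The 10% is then compensated twice.

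The 40 itself was not reproduced from the stated inputs (f = 0.318, power 0.80, alpha 0.05, 3 groups, 2 measurements, correlation 0.75). With drop-out added, the group-by-time interaction gives 20 in total and the between-group test 97. That is a separate matter, and nothing here depends on it.

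**3. Possible bias from analysing completers only**

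Let p be the fraction of a group that is lost, and d how much less far those people would have walked than that group's completers. The full-group mean is the completer mean minus p × d, so the completer mean is too high by p × d. For the between-group difference:

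net bias = (p × d in LUNARIS) − (p × d in comparator)

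The protocol gives no value for d and no drop-out by group. I assume d = 100 m, with a range of 50-150 m. The planned 10% is 4 of 40 amputees. Spread over two groups of 20:

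| Lost (one group / other) | Difference in p | Net bias at d = 100 m | Range, d = 50-150 m |
|---|---|---|---|
| 2 / 2 | 0 | 0 m | 0 m |
| 3 / 1 | 0.15 − 0.05 = 0.10 | 10 m | 5-15 m |
| 4 / 0 | 0.20 | 20 m | 10-30 m |

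Losing 2 of 20 in one group and nobody in the other also gives 0.10 × d = 5-15 m. Over 10-20% loss in one group only, the range is therefore 5-30 m. The relevance threshold in Section 6.1 e) is 35 m.

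**4. Cross-check with a different model**

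Suppose one group loses its worst-tolerating fraction, and tolerance correlates r with distance. Under normality the completer mean rises by SD × r × φ(c) / (1 − p), where c is the p-quantile of the standard normal distribution. The protocol gives no SD, so I assume 60-120 m, with r = 0.3-1.0.

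- p = 0.10: factor 0.195, rise about 3.5-23 m.
- p = 0.20: factor 0.35, rise about 6-42 m.

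This is the same order of size as step 3.

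**The case against.** The strongest reply is that the protocol never says Section 7 m) overrides 7 a), and that the target in 6.3 c) could mean 40 enrolled and not 40 completed. A completer analysis is then one reading among several. This stands: that Section 7 m) governs is an inference from its being the more specific text, and from its fit with the top-up and with the end-of-study definition. The contradiction remains on any reading.

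A reader might go further and infer that the plan favours a poorly tolerated foot, or favours the LUNARIS. The document does not support that. It gives no drop-out by group and no link between leaving and distance, and people may withdraw without giving a reason. The sign depends on which group loses more and on who leaves; with equal loss and equal deficit the bias is zero.

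Two other inferences also fail. Replacement does not hide the loss, because Section 7 m) requires drop-outs to be recorded. Nor does it clearly break the allocation blocks: Section 7 e) mentions a block size of 4, but Section 6.3 e) says the study is non-randomised, and nothing says a late recruit takes a leaver's place. For the same reason, retaining everyone does not by itself make the groups comparable.

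It can also be said that missing-data methods belong in a statistical analysis plan. That is fair for technical detail. Here, however, the protocol itself fixes an exclusion rule and rules out sensitivity analysis.

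**Conclusion.** The point holds as a contradiction that must be resolved before outcome data are seen: Sections 7 a) and 7 m) give opposite analysis sets for the primary endpoint, and Sections 6.1 f), 6.3 c) and 7 e) do not agree on replacement or on what 40 means.

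If Section 7 m) governs and 6.3 c) means completers, the primary analysis is a completer analysis with no planned check. The bias this can cause is conditional. It runs from zero, with equal loss and deficit, to 5-30 m in the mean of one group if 10-20% of that group alone are lost and would have walked 50-150 m less. Those deficits and the one-sided loss are assumptions. The need for the change rests on the contradiction and on the discarded walks, not on any particular number of metres.

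**What to change.** Delete the exclusion of drop-outs from Section 7 m) and reconcile Sections 6.1 f), 6.3 c), 7 a) and 7 e) into one rule:

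- All allocated amputees are analysed in their allocated group. The mixed model uses every available 6-minute walk, at week 12, week 24 or both. Able-bodied subjects with a walk are likewise retained.
- Forty is the number of amputees allocated, including the 10% drop-out allowance. Those who drop out are not replaced.
- Section 7 n) names one sensitivity analysis that varies the assumed outcome of drop-outs separately in each group, including unequal assumptions. This matters most for people lost before week 12. No walk is measured before allocation, so they have no distance for the model to use, and imputing one from pre-allocation variables would add little.
- Drop-out is reported by group, with reasons.

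The cost is wording and one extra analysis, with no additional participants. The downside is about 36 complete cases instead of 40 at 10% drop-out. For an analysis of complete cases alone, standard errors would be larger by a factor of √(40/36) = 1.05, about 5%; the retained week-12 walks recover part of that.

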## 6. Design of the clinical investigation

### 6.1. General

#### a) Description of the design type of clinical investigation to be performed

This cohort study includes three groups.

- 20 lower-limb amputees who are going to do their rehabilitation and perform daily activities with a new articulated ankle foot prosthesis: the LUNARIS®.
- 20 lower-limb amputees who are going to do their rehabilitation and perform daily activities with a conventional prosthetic ankle: the SACH® followed by the most suited prosthesis for them.
- 20 able-bodied subjects which will be used as a control group.

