##### Protocol:

Figure 2 provides a visualisation of the investigation workflow.

[figure not shown]

Figure 2: Overview clinical trial. MRI: Magnetic Resonance Imaging, PEQ: Prosthetic Evaluation Questionnaire, ADL: Activities of Daily Living

The clinical investigation will comprise 4 test days for participants with a lower limb amputation and 2 days for the control group of able-bodied individuals.

The able-bodied individuals will undergo an MRI-scan at the University hospital Brussels (dpt. Radiology and Magnetic Resonance) and then perform functional performance tests.

Participants with a lower limb amputation will start the clinical investigation upon the start of their rehabilitation. At week 0, when initiating the rehabilitation, participants will undergo a baseline MRI-scan at the University hospital Brussels (dpt. Radiology and Magnetic Resonance). Then, they will be allocated to the one of the treatment arms (LUNARIS® or the SACH® foot) and will conduct their rehabilitation to learn walking with a prosthesis. At the end of the rehabilitation, after 12 weeks, participants will perform baseline functional performance tests, fill out the prosthetic evaluation questionnaire (PEQ) measuring quality of life [11] and fill out the Mini-Mental State Examination to account for cognitive impairments and onset of Alzheimer's Disease [12]. Between weeks 12 and 24 of the clinical investigation (i.e. intervention period), participants will perform their daily activities with the allocated prosthesis. During this 12-week period, trying out new prosthetic devices will be allowed within the group of individuals wearing the SACH® foot as this is considered the usual care. At the end of this period (after week 24), post-test assessment will take place and participants will undergo the same MRI and functional performance tests as during the baseline assessments to evaluate the changes that occurred. Additionally, the participant will be asked to fill out the Quebec User Evaluation of Satisfaction with assistive Technology (QUEST 2.0) to assess prosthetic satisfaction [25-27]. The 12-week intervention period is chosen based on a study examining the effect of 12 weeks balance training in healthy and older adults on neuroplasticity and on the accommodation time to walking with a new prosthesis [13][14][15].

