## 6.2. Investigation device(s) and comparator(s)

### a) Description of the exposure to the investigational device

20 subjects are asked to do their rehabilitation process with the LUNARIS® and then to perform their daily activities with the LUNARIS® during a period of 6 months in total. They are also asked to perform the above mentioned activities with the LUNARIS® during 2 experimental sessions.

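### Sections 7 m and 6.3 c, followed as written, give a completers-only comparison with replacement, contrary to 7 a and 6.1 f, and nothing provides for testing a subject who stops LUNARIS

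*Protocol*

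**What the plan says.** On who is analysed, the protocol gives two answers. Section 7 a: "The entire population enrolled in the study will be included in the analysis". Section 7 m: "Drop-outs and unused data will not be included in the analyses". Neither drop-out nor unused data is defined, and 7 n plans no sensitivity analysis.

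On replacement it also gives two answers. The item "Any procedures for the replacement of subjects" (6.1 f) is marked not applicable. Section 6.3 c says that "additional subjects will be recruited via the same rehabilitation centres and orthopaedics departments of hospitals until the sample size is obtained", meaning 40 amputees and 20 able-bodied subjects. The condition that opens that sentence is garbled, so it is unclear exactly when recruitment is triggered. The 40 in 7 e already allows for 10% drop-out.

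On the feet worn:

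- **Control arm.** Section 6.1 a defines it as "the SACH® followed by the most suited prosthesis for them". Section 6.1 d adds that in weeks 12 to 24 "trying out new prosthetic devices will be allowed within the group of individuals wearing the SACH® foot as this is considered the usual care". Section 6.2 b has these subjects tested on the prosthesis that suits them best.
- **LUNARIS arm.** Section 6.2 a asks subjects to use LUNARIS for rehabilitation and daily activities, and continues: "They are also asked to perform the above mentioned activities with the LUNARIS® during 2 experimental sessions". No other foot is mentioned for them.
- **Withdrawal.** Section 6.3 c says "Participants can withdraw at any time without reason from the experiment". It does not mention stopping the foot while remaining in the study.

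**The concern.** The two contradictions alone leave the analysed group open. The operational statements (7 m removes drop-outs, 6.3 c recruits more subjects) lead to a comparison of those who completed, with those who left replaced by newcomers.

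The difference between the arms adds to this. A control subject who changes foot is following the assigned strategy and is still tested. A LUNARIS subject who gives up the foot has no described route to the remaining tests. If such a subject is not tested, or the result is set aside as unused, the LUNARIS mean describes only those who stayed on the device.

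The bias could go either way. If poorer walkers stop, the remaining LUNARIS mean is too high. If the most active of the K3-K4 subjects admitted by 6.3 a stop a foot that section 2 a describes as supporting low to moderate impact, it is too low. No part of the protocol reports either pattern. A week-24 distance that was never measured cannot be recovered later.

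**Working it through.** **Step 1: the rules side by side.**

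| Question | One statement | Other statement |
|---|---|---|
| Who is analysed? | 7 a: all enrolled | 7 m: not drop-outs or unused data |
| Are subjects replaced? | 6.1 f: not applicable | 6.3 c: recruit until 40 and 20 are reached |
| Foot at the tests | Control (6.2 b): the most suited one | LUNARIS (6.2 a): LUNARIS |
| Tests after a change of foot | Control: yes (6.1 a, 6.1 d, 6.2 b) | LUNARIS: not addressed |

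**Step 2: inputs for an illustration.** The protocol gives no figure for this effect, no rate of stopping LUNARIS and no walk distances.

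- Arm size 20 (6.1 a).
- Relevance threshold 35 m (6.1 e).
- Drop-out allowance 10% (7 e). For one arm, 0.10 x 20 = 2 subjects. This is a drop-out figure, not a device-stopping rate; it is borrowed only to choose k.
- Assumed: k subjects stop LUNARIS and are excluded.
- Assumed: D is the mean week-24 distance M of those still on LUNARIS, minus what the stoppers would have walked on the foot they then wear. D may be positive or negative; sizes of 35 to 100 m are shown.

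**Step 3: formulas for the raw LUNARIS mean.**

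- Without replacement: M - [(20 - k)M + k(M - D)]/20 = (k/20) x D.
- With replacement to 20 completers, assuming replacements resemble the other completers: M - [20M + k(M - D)]/(20 + k) = k/(20 + k) x D.

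**Step 4: results for k = 2.** The sign follows the sign of D.

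| Size of D | Without replacement | With replacement | Share of 35 m |
|---|---|---|---|
| 35 m | 2/20 x 35 = 3.5 m | 2/22 x 35 = 3.2 m | 10% / 9% |
| 50 m | 5.0 m | 4.5 m | 14% / 13% |
| 100 m | 10.0 m | 9.1 m | 29% / 26% |

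For k = 1 and D = 100 m the shift is 5.0 m without and 4.8 m with replacement. A shift of the full 35 m at D = 100 m needs 35 x 20/100 = 7 stoppers without replacement, or 35 x 20/(100 - 35) = 10.8, so 11, with it.

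**Step 5: what the planned model could change.** Section 7 b plans a mixed model with baseline covariates, and 7 e assumes a correlation of 0.75 between the two measurements. Suppose the stoppers' gap is already fully present at week 12, variances are equal at the two visits, and the week-12 distance is adjusted for. Then about 1 - 0.75 = 25% of the raw shift remains: 10 m becomes about 2.5 m. A pure change contrast would remove it entirely. Neither helps with a gap that opens after week 12. Nor do they help with a subject who stops during rehabilitation and is never tested: functional testing first takes place at week 12 (6.1 d, 6.4 a), so that subject has no walk distance.

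**The case against.** The strongest reply is that the protocol is silent about LUNARIS stoppers and does not mishandle them. Section 6.1 d has participants take the week-24 tests without requiring that they still wear the allocated foot, 6.2 a only asks them to use LUNARIS, and 7 a read literally keeps everyone in. This stands. A reader might infer that a subject who stops LUNARIS is a drop-out and is removed by rule. No section says so, and none bars that subject from testing.

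A reader might also infer that one event, a foot that does not suit, is treated in opposite ways in the two arms. The text does not support that. Control subjects move on from SACH as a planned part of usual care, with no condition that the foot has failed them, whereas a LUNARIS subject who stops departs from the assignment. The asymmetry follows from comparing one device with a strategy, a choice that the protocol states openly.

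It can further be said that H1 (section 5 d) asks about people walking with LUNARIS, so part of the shift calculated above is the distance between two questions and not an error. That is fair, and it is why an on-device analysis should be kept. However, the purpose in section 5 a is to compare rehabilitation with LUNARIS and with usual feet, which the strategy comparison answers.

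Finally, an analysis plan could define drop-out and settle the analysis sets. That also stands, so it would be too strong to say that a later plan could repair none of this. It could not supply tests that were not done. The contradictions between 7 a and 7 m, and between 6.1 f and 6.3 c, remain whatever such a plan says.

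**Conclusion.** The point holds in a limited form. Two contradictions are certain: who is analysed (7 a against 7 m) and whether subjects are replaced (6.1 f against 6.3 c). Following 7 m and 6.3 c gives a completers-only comparison. That LUNARIS stoppers would be lost from it is possible and not fixed by the text; the gap is that nothing provides for testing them.

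The direction of any bias is unknown and its size cannot be derived from the protocol. With 2 of 20 stopping and a gap of 35 to 100 m, both assumed, the raw LUNARIS mean moves by about 3.5 to 10 m, or 10% to 29% of the 35 m threshold. Replacement makes this slightly smaller, and covariate adjustment could make it much smaller. It would be wrong to infer that this could by itself produce a 35 m difference: even at a 100 m gap, 7 of the 20 LUNARIS subjects would have to stop. The case for acting before enrolment is that the remedy is cheap and the missing tests cannot be done afterwards.

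**What to change.** - **6.3 c:** separate stopping the allocated foot, with date and reason recorded, from leaving the study.
- **6.2 a:** state that a subject who stops LUNARIS attends whichever of the week-12 and week-24 tests remain, on the foot then worn.
- **7 m:** replace the exclusion with a rule that every enrolled amputee subject with any walk distance enters the mixed model in the allocated group. Word 7 a to match.
- **6.1 f and 6.3 c:** give one replacement rule, under which stopping the foot does not trigger replacement.
- **Supplementary analysis:** keep a comparison restricted to subjects still on LUNARIS, for H1. It will again be a selected group.

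The cost is wording in five places and one data field (date and reason), with no extra type of visit and no larger sample. The real downside is that the primary contrast becomes starting rehabilitation with LUNARIS against usual care, and not wearing LUNARIS throughout. This matches the purpose in section 5 a and the control arm as defined in 6.1 a. The change does not remove bias from non-randomised allocation (6.3 e); that is a separate matter.
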